### Intervention

Preoperative data collected will include patient demographics and comorbidity conditions (genitourinary, cardiac, pulmonary, gastrointestinal, renal, or rheumatologic) and a detailed history of symptom onset.

The procedure was performed by a surgeon that had performed at least 50 LCs.

On admission, the patients were started on cefotaxime, 2 g IV every 12 h, which was continued postoperatively according to NNISS score.

The standard four-trocar operative technique is used for LC for acute cholecystitis.

When the gallbladder is distended it will be first aspirated. To allow a good hold on the gallbladder larger graspers will be inserted through a 5 mm right lower port. The cystic artery and duct are clip-ligated in the MD group whereas in the H group cystic artery and duct are closed by H. In the H group the surgeon will use only H, whereas in the MD group the surgeon will use only MD. The gallbladder and intraperitoneal "dropped" stones are collected in an endoscopic bag and extracted through the umbilical cannula site, which can be extended. A closed system suction drain is left. Fascial closure is attempted only at the umbilical cannula site. The skin at all the cannula sites are closed with staples. Conversion to laparotomy will be decided by the operating surgeon and each conversion will be motivated.

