# The HAC Trial (Harmonic for Acute Cholecystitis) Study. Randomized, double-blind, controlled trial of Harmonic(H) versus Monopolar Diathermy (M) for laparoscopic cholecystectomy (LC) for acute cholecystitis (AC) in adults

**DOI:** 10.1186/1745-6215-10-34

**Published:** 2009-05-26

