### Statistical Methods and Power Calculations

By using StatCal of Epi INFO 2000 software package (Centers for Disease Control and Prevention, Atlanta, GA, USA), a sample size of 21 patients for each group (42 patients for the whole study) has been calculated to reach a confidence level of 95% with a power of 80%, supposing that the hospital stay for LC with H the conversion rate can be reduced from 35% to 3%.

Analysis of data is by intention-to-treat. It will be specified when and how any deviations from randomised allocation, false inclusions, or missing outcomes have been handled. Repeated measures of the outcome will be performed with complete case analyses, potentially excluding individuals with some follow-up data, Eventual missing outcomes will be imputed using baseline values or by assuming that all missing participants have the same risk as the observed participants in the control group.

Data are expressed as numbers (%) and means (SD). The results of the two groups in comparison are analyzed using the Pearson's chi-square test and Fisher exact test, as appropriate, for proportions in case of discrete data. Fisher exact test is used when the data are very unequally distributed among the cells of the table or the expected frequency of any cell is less than 5 or the total N is less than 50. For means in case of continuous numerical data, the independent samples T test and the Mann-Whitney U-test are used, respectively for data normally and non-normally distributed. The data are previously tested for normality by the Kolmogorov-Smirnov test. For multivariate analysis the stepwise logistic regression is applied. A *p*-value of < 0.005 is in any case considered to be statistically significant.

Forward selection has been used as variable selection method; it will include all the baseline variables and all baseline variables are assessed for imbalance. The final model only contain variables with a p-value less than 0.05. Imbalances of baseline variables are defined comparing the groups using t tests for continuous variables and χ^2 ^tests for categorical variables. The adjustments are based upon the stratified logrank test or analysis of covariance. [11-13]The primary outcome is the conversion rate. Secondary outcomes are: intra-operative and post-operative morbidity and mortality, operative time and intra-operative blood losses.

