### Data Collection

Patients' data sheets are generated containing demographic data and preoperative, operative, and postoperative information.

Pre-operative notes concern the history of gallbladder stones, the presence of associated diseases (cardiac, hypertension, diabetes, malignancy), duration of gallbladder complaints (as an indication for the onset of the disease), finding of a palpable gallbladder, temperature, and laboratory results of WBC count, serum bilirubin, gamma GT, CRP, IL-6 and alkaline phosphatase.

Ultrasound findings are also reported.

Operative data of concern are macroscopic findings (of acute cholecystitis, gangrenous cholecystitis, hydrops, and empyema of the gallbladder), the presence of small stones (< 1 cm diameter) or large bile stones (> 1 cm diameter), information regarding perforation of the gallbladder and intraperitoneally "lost" stones, reasons for conversion, and duration of surgery. Postoperative notes of interest included the use of nasogastric tubes and drains, the amount of analgesics used, (evaluation of pain with VAS score), complications, and length of hospital stay.

Complications are classified as surgical infections (wound infection, subphrenic or subhepatic abscess); noninfectious surgical problems (e.g., bile duct injury, hemorrhage); remote infections (urinary or respiratory); and miscellaneous problems (e.g., atelectasis, deep vein thrombosis, AMI, CVA, etc). The collected information are entered into a database as either continuous or categorical variables for statistical analysis. Following the operative procedure, a normal sterile dressing will be applied to cover the abdomen.

A second surgical team, aware of the operative findings but not the surgical dissection instrument, then will assume the care of the patient. Postoperative care and ability to be discharged from the hospital will be determined by the second surgical team. The primary operative team will be in every moment available for emergent consultation.

Patient discharge will be base on good medical practice criteria: 1) apyrexia 2) absence of diseases requiring hospitalisation 3) return of bowel function 4) patient's compliance.

No Placebo drugs are used for this study.

Every patient will be asked to sign the Informed Consent.

In the informed consent form, patients will receive all the information about the study protocol, the confidential nature of personal data and will fill up a questionnaire before signing or refuse.

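### The title says double-blind, but the primary outcome is decided in theatre by an operator who knows the instrument, and the only masking described begins after surgery

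*Protocol article*

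**What the plan says.** The title reads "Randomized, double-blind, controlled trial of Harmonic(H) versus Monopolar Diathermy (M" and so on. The opening of Methods calls the study only prospective and randomized.

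Under Statistical Methods and Power Calculations: "The primary outcome is the conversion rate".

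Under Intervention, on who knows the arm: "In the H group the surgeon will use only H, whereas in the MD group the surgeon will use only MD". The arms also differ visibly in the operative field: "The cystic artery and duct are clip-ligated in the MD group whereas in the H group cystic artery and duct are closed by H". On who determines the primary outcome: "Conversion to laparotomy will be decided by the operating surgeon and each conversion will be motivated".

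Under Data Collection, after the abdomen has been covered with a dressing: "A second surgical team, aware of the operative findings but not the surgical dissection instrument, then will assume the care of the patient". That team's remit is then given: "Postoperative care and ability to be discharged from the hospital will be determined by the second surgical team". The same section lists reasons for conversion among the operative data and says that the collected information goes into a database for statistical analysis. Whether the patient is masked is not stated.

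**The concern.** The label promises a protection that the design does not give to its main outcome. Conversion is a judgement made during the operation by the person holding the instrument under test, in a trial whose stated aim is to show that Harmonic (H) lowers conversion compared with monopolar diathermy (MD). A surgeon who persists a little longer with H, or opens a little sooner with MD, produces a lower H conversion rate without any device effect. Operative time, blood loss and intra-operative morbidity also arise before the masked team is involved.

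A reader who takes double-blind at face value would discount this route to bias in the primary result, when it is the first thing to consider.

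**Working it through.** **1. Masking, outcome by outcome**

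| Outcome | When it is fixed | Who determines it | Masked, per the article? |
|---|---|---|---|
| Conversion (primary) | During surgery | Operating surgeon | No |
| Operative time, blood loss, intra-operative morbidity | During surgery | Arise in theatre, before hand-over | No |
| Post-operative care and discharge | After hand-over | Second team | Yes |

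The label therefore fails for the primary outcome and for every intra-operative secondary outcome. It is supported for decisions on post-operative care and discharge.

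**2. Inputs from Statistical Methods and Power Calculations**

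- Conversion 35% (MD) against 3% (H), 21 per group, 95% confidence, 80% power.
- Fisher's exact test when the total is below 50, so it applies to 42 patients.
- An analysis threshold of p<0.005, which does not match the 95% confidence level used for the sample size. That conflict is a separate matter; both thresholds are used here.

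**3. The plan's own sample size** (two-sided 0.05, power 0.80, so z = 1.960 and 0.842; sidedness is not stated and two-sided is assumed)

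- Unpooled variance: n = (1.960 + 0.842)² × (0.35×0.65 + 0.03×0.97) / 0.32² = 19.7, so 20 per arm.
- Pooled variance, mean rate 0.19: n = [1.960√(2×0.19×0.81) + 0.842√(0.35×0.65 + 0.03×0.97)]² / 0.32² = 22.4, so 23 per arm.

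The stated 21 lies between the two and is accepted.

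**4. What unmasked discretion could do**

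Assume a true rate of 35% in both arms (no device effect), and let discretion lower only the recorded H rate, to 20% or 15%. With 21 per arm, sum over all tables with a MD conversions and b H conversions:

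P(false pro-H result) = Σ Bin(a; 21, 0.35) × Bin(b; 21, p_H), over tables with a > b and two-sided Fisher p below the threshold.

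| Recorded H rate | p<0.05 | p<0.005 |
|---|---|---|
| 35% (no shift) | 1.1% | 0.1% |
| 20% (assumed) | 11.5% | 1.9% |
| 15% (assumed) | 21.8% | 4.5% |

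**5. How far one decision matters**

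Expected conversions under the planned rates are 21×0.35 = 7.35 (MD) and 21×0.03 = 0.63 (H). Two-sided Fisher p, MD v H:

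- 7 v 1: (C(21,7)×21 + C(21,8)) / C(42,8), doubled by symmetry, = 2 × (2,441,880 + 203,490) / 118,030,185 = 0.0448.
- One fewer in MD, 6 v 1: 0.0931. One more in H, 7 v 2: 0.1300. Either change crosses 0.05.
- 7 v 0: 0.0086. One fewer in MD, 6 v 0: 0.0207. One more in H, 7 v 1: 0.0448. Neither change crosses 0.05.
- At 0.005, 7 v 1 is already non-significant and neither 6 v 1 nor 7 v 2 alters that. Flips occur elsewhere: 8 v 0 (0.0034) to 7 v 0 (0.0086), and 10 v 1 (0.0036) to 9 v 1 (0.0089).

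Over all tables under the planned rates, the chance of ending within one conversion of the boundary is about 44% at 0.05 and 42% at 0.005.

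**The case against.** **The operator cannot be masked to the instrument.** True, and this stands. The fault is not a failure to blind the surgeon. It is a label that claims more than the design delivers, and a label can be changed.

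**The Methods are open about it.** Also true: who decides conversion and when masking starts are both set out, and Methods does not repeat the label. A careful reader is not misled. But the title is what indexes and summaries carry forward, and it conflicts with the Methods on the outcome that carries the trial's aim.

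**Reasons for conversion are already collected.** A reader might infer that these reasons lie unused. The article does not support that: Data Collection sends them to the database for analysis. Nor does it say who completes the data sheet. What is absent is any review of the reasons by someone masked.

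**The size can be overstated.** A reader might infer that one conversion decides the trial. It does so for some tables only. Zero is the most likely H count under a 3% rate (0.97²¹ = 53%, against 34% for one), and 7 v 0 survives one change in either arm at 0.05. Such fragility also comes from having 42 patients and not from the lack of masking. Quoting 0.05 alone would likewise exaggerate, since the stated p<0.005 gives much smaller probabilities.

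**The safeguard is incomplete.** This stands. A conversion avoided by persisting with H leaves no event, no reason and nothing to classify, and the reasons still originate with an unmasked decision-maker.

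**Conclusion.** The point holds as a mislabelled design with an unmasked primary outcome. The title claims a property that the trial lacks for conversion and for all intra-operative outcomes; the masking that exists covers post-operative care and discharge. Nothing in the article shows that surgeons would in fact convert differently by arm, so this is an exposure to bias and not evidence of it.

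The size is illustrative. If discretion lowered recorded H conversions from a common 35% to 20% or 15%, the false pro-H probability would rise from 1.1% to 11.5% or 21.8% at 0.05, and from 0.1% to 1.9% or 4.5% at 0.005. The shifts are assumptions, and the documents give no basis for choosing among them. A single conversion can change the conclusion in some plausible tables but not in all.

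The trial remains usable. The label should be corrected, and the primary conclusion should be read as coming from an open assessment.

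**What to change.** 1. **Correct the label.** Replace double-blind in the title with a statement of who is masked and for which outcomes: second team masked for post-operative care and discharge; operator and all intra-operative outcomes, including the primary, open. Say whether patients are masked. Qualify the primary conclusion accordingly. The cost is a wording change and a less favourable design label.

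2. **Add a partial safeguard.** Record the reason for each conversion, when the decision is made, in categories defined in advance. Have the second team classify each conversion as forced or discretionary, under definitions that the investigators fix beforehand, from a note with instrument and clip details removed. Pre-specify one sensitivity analysis of the primary outcome that counts only forced conversions, and report it beside the main result. State with it that it addresses early MD conversions and cannot detect conversions avoided by persisting with H. The cost is a one-page form, a few minutes per conversion (about 8 are expected in total, 7.35 + 0.63) and one extra 2×2 table. No staff or patients are added, because the masked team already exists. The drawback is that the analysis removes events from an already small trial, so it should support the main analysis and not replace it.

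Neither step sets or implies a rule on when to convert.

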### Data Collection

Patients' data sheets are generated containing demographic data and preoperative, operative, and postoperative information.

Pre-operative notes concern the history of gallbladder stones, the presence of associated diseases (cardiac, hypertension, diabetes, malignancy), duration of gallbladder complaints (as an indication for the onset of the disease), finding of a palpable gallbladder, temperature, and laboratory results of WBC count, serum bilirubin, gamma GT, CRP, IL-6 and alkaline phosphatase.

Ultrasound findings are also reported.

Operative data of concern are macroscopic findings (of acute cholecystitis, gangrenous cholecystitis, hydrops, and empyema of the gallbladder), the presence of small stones (< 1 cm diameter) or large bile stones (> 1 cm diameter), information regarding perforation of the gallbladder and intraperitoneally "lost" stones, reasons for conversion, and duration of surgery. Postoperative notes of interest included the use of nasogastric tubes and drains, the amount of analgesics used, (evaluation of pain with VAS score), complications, and length of hospital stay.

Complications are classified as surgical infections (wound infection, subphrenic or subhepatic abscess); noninfectious surgical problems (e.g., bile duct injury, hemorrhage); remote infections (urinary or respiratory); and miscellaneous problems (e.g., atelectasis, deep vein thrombosis, AMI, CVA, etc). The collected information are entered into a database as either continuous or categorical variables for statistical analysis. Following the operative procedure, a normal sterile dressing will be applied to cover the abdomen.

A second surgical team, aware of the operative findings but not the surgical dissection instrument, then will assume the care of the patient. Postoperative care and ability to be discharged from the hospital will be determined by the second surgical team. The primary operative team will be in every moment available for emergent consultation.

Patient discharge will be base on good medical practice criteria: 1) apyrexia 2) absence of diseases requiring hospitalisation 3) return of bowel function 4) patient's compliance.

No Placebo drugs are used for this study.

Every patient will be asked to sign the Informed Consent.

In the informed consent form, patients will receive all the information about the study protocol, the confidential nature of personal data and will fill up a questionnaire before signing or refuse.

There will be not inconveniences caused to the patients. No incentives are planned for the patients regarding the operation or the follow-up.

All the medical informations obtained from the patients will be kept confidentially among the research scientists conducting the study.

The patients will be free to withdraw from the study, whenever they want without any obligation.

The study will be stopped in case of newly discovered statistically significant advantages in one group.

The aim of the study is to demonstrate that H can reduce conversion rate compared to MD in LC for AC but also differences in terms of morbidity, mortality, operation time, hospital stay, postoperative pain, return to normal activity will be evaluated.

The primary endpoints of our study will be:

**A) **To evaluate the conversion rate

**B) **To evaluate morbidity, mortality, operation time

**C) **To evaluate hospital stay, postoperative pain, return to normal activity

The onset of any other complications will be recorded intraoperatively, postoperatively, at discharge, at 7-days, 1-month and 6-months.

The side effects that could have observed are not substantially different between the arms of the study.

All the above mentioned data will be recorded in the Case Report Form and later stored in computer database. At the end of the study the final statistical examination will be carried out.

An interim statistical examination of the data will be done every 3 months during the period of patients' inclusion in the study. Then at the end of every completed follow-up period (1-month, 6-months).

The statistical analysis will be carried out using Epi Info 2000, Version 1.1 software package (Dean AG, Arner TG, Sangam S, Sunki GG, Friedman R, Lantinga M, Zubieta JC, Sullivan KM, Smith DC. Epi Info 2000, a database and statistics program for public health professionals for use on Windows 95, 98, NT, and 2000 computers; Centers for Disease Control and Prevention, Atlanta, Georgia, USA, 2000)

No incentives are planned for the patients regarding the operation or the follow-up.

The study will take approximately 6 months – 1 year for the inclusion period. According to the number of AC managed monthly, the duration of the inclusion period can be approximately of 1 year to reach the number of about 42 enrolled patients.

An interim report is planned at the end of any completed follow-up period.

The trial has been registered with the ClinicalTrials.gov Identifier: NCT00746850 .

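### The plan binds the trial to stop on plain statistical significance at repeated looks, with no interim boundary and no deciding outcome, so its false-positive rate is undefined and any early stop overstates the effect

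*Protocol article*

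**What the plan says.** All the interim provisions are in the Data Collection section of the protocol article. The stopping rule reads: "The study will be stopped in case of newly discovered statistically significant advantages in one group". The schedule reads: "An interim statistical examination of the data will be done every 3 months during the period of patients' inclusion in the study", followed by further examinations when the 1-month and 6-month follow-up periods are complete. On duration: "The study will take approximately 6 months – 1 year for the inclusion period". A later sentence adds: "An interim report is planned at the end of any completed follow-up period".

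Two other statements bear on how the rule would be applied.

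- **Outcome.** Statistical Methods and Power Calculations names the conversion rate as the primary outcome. Data Collection lists as primary endpoints conversion, morbidity, mortality, operation time, hospital stay, postoperative pain and return to normal activity, which makes seven.
- **Threshold.** Statistical Methods says: "A *p*-value of < 0.005 is in any case considered to be statistically significant". The same section says the sample size "has been calculated to reach a confidence level of 95% with a power of 80" per cent, which implies a significance level of 0.05.

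**The concern.** The rule is an instruction to stop, and its trigger is ordinary significance at whichever look it appears. A separate analysis plan could not merely fill this in; it would have to override it. Whoever applies the rule must first decide which outcome counts and which p-value counts, and the article supports two answers to each question.

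Three things are at stake. Repeated testing without a boundary leaves the overall false-positive rate unset. A trial this small that stops at its first significant result will report a difference well above the true one. And the stated aim is fewer conversions without a significant increase in morbidity: stopping after 10 to 32 of the 42 patients leaves even less information on morbidity.

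**Working it through.** **Inputs from the article.** Conversion 35% with monopolar diathermy and 3% with Harmonic; 21 patients per group; 95% confidence; 80% power; Fisher's exact test whenever the total is below 50, hence at every look; inclusion of 6 to 12 months with a look every 3 months.

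**Assumptions.** Even accrual, so that four looks fall at 5, 10, 16 and 21 per arm, and two looks at 10 and 21. For the seven-outcome reading: three binary outcomes by Fisher's test (35%, 20% and 1%), four continuous outcomes by t test, and correlation between outcomes of 0 to 0.6. The article gives no morbidity or mortality rate and no correlation.

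**1. The plan's own sample size.** Two-sided 0.05, power 80%.

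- Unpooled variance: n = (1.96 + 0.842)² × (0.35×0.65 + 0.03×0.97) / 0.32² = 7.85 × 0.2566 / 0.1024 = 19.7, so 20 per group.
- Pooled variance, mean rate 0.19: n = [1.96×√(2×0.19×0.81) + 0.842×√0.2566]² / 0.1024 = 22.4, so 23 per group.
- The stated 21 lies between these. With 0.005 (z = 2.807) the pooled formula gives 38.4, so 39 per group. The trial was therefore sized at 0.05, not at the written 0.005.

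**2. What can trigger a stop on conversion by Fisher's test.** At 5 per arm the most extreme table, 5/5 versus 0/5, has p = 2/252 = 0.0079. At 0.005 no binary outcome can cross at that look. At 0.05 the smallest difference that crosses is 4/5 versus 0/5, or 80 points (p = 2 × 5/210 = 0.048).

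**3. Chance of a significant result when the arms do not differ.** Conversion (35% in both arms) by exact enumeration of the sequential tests; seven outcomes by simulation.

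| Reading | Level | Four looks, ever | Before the last look | Two looks, ever |
|---|---|---|---|---|
| Conversion, Fisher | 0.005 | about 0.3% | 0.2% | 0.3% |
| Conversion, Fisher | 0.05 | 4.8% | about 3.8% | 3.0% |
| Any of seven | 0.005 | about 6% | about 5% | 3–4% |
| Any of seven | 0.05 | 40–48% | 34–42% | 27–34% |

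For comparison, a single final test gives 2.1% for conversion at 0.05 and about 19–22% for any of seven outcomes at 0.05. That second figure is ordinary multiplicity of endpoints; only the excess over it comes from repeated looks.

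**4. Exaggeration after an early stop.** Conversion only, Fisher's test, four looks; an early stop means one of the first three.

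| True rates | Level | Stopped early | Mean observed difference |
|---|---|---|---|
| 35% vs 3% (32 points) | 0.05 | 55% | 46 points |
| 35% vs 3% (32 points) | 0.005 | 11% | 57 points |
| 35% vs 15% (20 points, assumed) | 0.05 | 17% | 51 points |
| 35% vs 15% (20 points, assumed) | 0.005 | 2% | 59 points |

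Under the plan's own rates the overstatement is 46 − 32 = 14 points at 0.05 and 57 − 32 = 25 points at 0.005. The stricter level makes early stops rarer but each one more extreme.

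**The case against.** The strongest reply is that the article calls p < 0.005 the level in any case. Read literally, that covers the stopping rule too, and it is stricter than a four-look Pocock level (about 0.018). Conversion is also the stated aim and the one outcome called primary in the statistical section. On that reading the false-positive rate is about 0.3%, and even at 0.05 Fisher's test holds it to 4.8%. This stands. A reader might infer from the bare rule that a chance stop is likely; the article does not support that, because the 40–48% figure needs both the 0.05 level and a stop on any listed outcome. It also takes the upper end of the number of looks, includes the look at full accrual, where nothing is cut short, and contains endpoint multiplicity that a single final test would have as well.

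Three smaller points also stand. The article does not say who sees the interim comparisons, so that they are unblinded is only an inference. The 1-month and 6-month examinations come after inclusion and can neither shorten enrolment nor add conversion data. And newly discovered advantages could conceivably mean outside evidence, although the trial's own 3-monthly examinations are the natural source.

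What the reply does not remove: 0.005 is not presented as an interim adjustment and is not the level the trial was sized for; the rule names no outcome while the same section lists seven as primary; and exaggeration after an early stop occurs even on the most favourable reading.

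**Conclusion.** The point holds as a badly fixed stated rule. The trial must stop on significance, but the article does not settle at which level, on which outcome or against which interim boundary. The false-positive rate is therefore not set by the design: with four looks it runs from about 0.3% to 40–48% across readings that the text allows. The low end is the literal threshold applied to conversion. The high end should not be quoted as the expected risk, and it rests on assumed outcome rates and correlations.

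The firmer conclusion concerns the estimate, since it needs only conversion, the prescribed test and the plan's own rates, with even accrual over four looks. If 0.05 is applied and the design assumption is true, an early stop is more likely than not (55%). At 0.005 it is uncommon (11%), with a larger overstatement when it happens.

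**What to change.** Amend the interim paragraphs before the first look:

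1. Name the conversion rate as the only outcome that can stop the trial for efficacy.
2. State the number of efficacy looks and a strict interim boundary, for example one look at about 10 per arm with p < 0.001 (Haybittle-Peto).
3. Make the other 3-monthly reviews safety tabulations without between-arm efficacy testing.
4. State that the 1-month and 6-month reports cannot trigger stopping.
5. Reconcile 0.005 with the 0.05 behind the sample size, and the single primary outcome with the list of seven. The final level should be chosen openly: 21 per group matches 0.05, whereas 0.005 would need about 39.

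The cost is a few sentences and, in practice, the loss of early stopping for efficacy. At 10 per arm, p < 0.001 by Fisher's test needs at least 8/10 versus 0/10 (p = 0.0007), which happens in about 0.4% of trials under 35% versus 3%. With the final Fisher test at 0.05, overall type I error is about 2% (2.1% with 35% in both arms) and power about 73%, the same as with no interim look. That power is below the planned 80% because of the prescribed Fisher test, not because of the boundary.
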